### Location and participants

The study will be conducted in three municipalities, providing a wide range of infrastructure, geography, and population. Participants will be children and youth (5–17 years old) injured while bicycling and seen at the Emergency Departments (EDs) of the main children’s hospitals in the cities (BC Children’s Hospital-Vancouver; Alberta Children’s Hospital-Calgary; Hospital for Sick Children-Toronto).

### Recruitment

We have an ED physician research team collaborator at each site. These site-investigators are members of Pediatric Emergency Research Canada; a network of clinicians performing multi-centre research projects. A research assistant will be at each site to work with the physician research team to plan and execute study recruitment that aligns with the local situation. A member of the healthcare team or ED research team will provide eligible participants with a study consent to contact/consent form. Study personnel will collect these forms regularly. If time permits and written consent is given by the bicyclist/parent, data collection may occur in the ED. Based on our previous ED research [14], we anticipate that most interviews will occur after the bicyclist is discharged, in which case an in-person interview will be arranged at the bicyclist’s home, hospital, or other convenient location. A written study assent form (for children) and/or consent form (for parents or older children/youth) will be completed before the interview. If an in-person interview cannot be arranged, a telephone interview along with verbal consent may be conducted. We will make a maximum of six call and five email attempts to contact injured bicyclists/parents at different times and on different days consistent with our previous research [14]. Obtaining some information by phone will reduce the likelihood of selection bias resulting from excluding bicyclists not interviewed in person. We have collected and mapped routes over the phone in previous work [58].

Given the focus on bicycling for transportation and the built environment, we will exclude (based on the Teschke et al. [24] study) those: 1) Who live or were injured outside of the participating cities; 2) With no known address or phone number; 3) Fatally injured; 4) Unable to communicate due to injury and lack of parental knowledge about route/crash details; 5) Who do not, and parents do not, speak English; 6) Injured on private property, 7) Injured while trick riding, mountain biking, racing, or riding in a mass bicycling event; 8) Who were riding a motorized bike, unicycle, tricycle, or tandem bike; and 9) Who had previously participated in the study. We will also exclude those who were not contacted and recruited within 3 months of the injury to decrease the likelihood of recall bias. We will keep a detailed account of the reasons for exclusion. We will not exclude those unable to remember all injury trip details, but will obtain as much information as we can about their personal and trip characteristics to assess the magnitude of any potential bias and to use in a sensitivity analysis whereby missing data are imputed.

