### Study design

We will use a case-crossover design to compare the built environment characteristics of the site where the injury event occurred (injury site) to those at two randomly selected sites (control sites) along the bicyclist’s route before the injury occurred. Our approach uses the design of a study of infrastructure and bicycling injury risk in adults [24]. It overcomes methodological limitations of previous bicycling injury research by controlling for important confounding by personal, weather, and daylight characteristics by using injured bicyclists on a single trip as their own controls, and addressing exposure to injury risk by comparing injury sites to control sites on the route bicycled on the injury trip.

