### Data collection

#### Interview and site selection

We will train a research assistant to conduct the interview using a semi-structured questionnaire to map the route of the injured bicyclist on the injury trip, including any trip continuation after the injury event. Detailed paper maps (including streets and off-street paths) will be used to identify the trip route and injury site. Using a digital map wheel, we will estimate the trip distance and multiply it by two randomly generated proportions to select two control sites along the route. The second of these points will be moved either forward or backward along the route (depending on participants study specific identification number) to match the intersection/non-intersection status of the injury site. We will ask questions on the circumstances of the injury event and characteristics of the injury and control sites on the trip such as street surface conditions, light conditions, presence of construction, and estimated speed. We will also collect data on personal characteristics (age, sex, bicycling experience etc.) and trip characteristics (type of bicycle, clothing colour, weather, time of day) for secondary analyses; the case-crossoverapproach inherently controls for these factors.

We will use the interview procedures and data collection forms that Teschke et al. used with adult bicyclists [24]. Our collaborators with expertise in child and youth injury prevention will modify the interview questions to ensure they were suitable for children and youth. The questionnaire and modifications were pilot tested with additional revisions made prior to initiation of the project.

Given that some children and youth will have mild to severe brain injuries, and that some information may come from very young children, the interviewer will record the source of the interview (child, parent, other proxy respondent, etc.) and rate their confidence in the quality of the interviewee’s description and recall of the bicycling route and site characteristics. We will conduct sensitivity analyses based on the interviewer’s trust in the information quality.

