### Data analysis

Route types will be classified into categories consistent with Teschke et al. [24] We will compare personal characteristics by age group: child (< 13 years old) and youth (13–17 years old) consistent with age categories used in our prior bicycling injury research [14, 59]. We will compare the characteristics of the injury and control sites accounting for the fact that we have matched data (i.e., the same subject contributes the injury and control sites along a given route) [60]. We will use conditional logistic regression analysis to examine the route characteristics related to bicycling injuries. We will add no more independent variables than 10% of the number of discordant pairs (case site location characteristics different than control site location characteristics) [61]. We have used this analytic approach in our previous work [62]. Multiple imputation analysis will be used to assess the influence of missing data on effect estimates [63].

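### Project 2D restricts where an injury site can lie but not where a control site can lie, so odds ratios are biased for features whose frequency differs between eligible and excluded places

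*Protocol article*

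**What the plan says.** Two rules in the Project 2D part of the protocol article bear on this.

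- **Injury sites (Recruitment).** The list of exclusions removes children "Who live or were injured outside of the participating cities" and, further down, those "6) Injured on private property, 7) Injured while trick riding, mountain biking, racing, or riding in a mass bicycling event". Item 6 and the city criterion concern place; item 7 concerns activity and is not at issue. An eligible injury site must therefore lie off private property and inside a participating city.
- **Control sites (Interview and site selection).** The interviewer is to "map the route of the injured bicyclist on the injury trip, including any trip continuation after the injury event". Then "we will estimate the trip distance and multiply it by two randomly generated proportions to select two control sites along the route". The second point is shifted along the route "to match the intersection/non-intersection status of the injury site". No other condition on a control site is given.

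The Project 2D Study design section describes the controls differently, as "two randomly selected sites (control sites) along the bicyclist’s route before the injury occurred"; the Abstract says the same. For the analysis (Data analysis), "We will use conditional logistic regression analysis to examine the route characteristics related to bicycling injuries".

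**The concern.** A case-crossover comparison treats the control sites as a sample of the places where the child was at risk of becoming a case. That holds only if an injury at a control site would have been counted. Here an injury on private land or beyond the city limit would have been excluded, yet a control point may fall there.

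Conditional logistic regression does not remove the problem. Self-matching deals with personal and trip factors, whereas this asymmetry lies between sites within each matched set. A larger sample does not reduce it, and neither the planned imputation nor the sensitivity analysis on interview quality addresses it.

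At stake are the odds ratios for route types and site features that are distributed differently in eligible and excluded places. Project 3B feeds the findings of Objectives 1 and 2 into the municipal toolkit, so such an odds ratio could be presented as evidence on the safety of a feature.

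**Working it through.** **1. The plan's own figures.** Project 2D, Sample size: 1139 × 0.49 = 558, and 558 × 1.5 = 837 injuries, which reproduces. With two controls each there are 2 × 837 = 1674 control sites. A matched case-control power formula (two-sided 0.05 assumed, OR 1.5, control prevalence 10%, two controls) gives 88% with no within-child correlation of exposure, 82% at correlation 0.2 and 77% at 0.3. The stated 80% is consistent with the 1:2 design for correlations up to 0.2. Sample size is not the difficulty.

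**2. Inputs for the bias.** The article gives none of the following, so all are assumptions:
- u = share of route length that is ineligible: 2%, 5%, 10%
- pe = prevalence of the feature in eligible places: 10%
- pi = prevalence in ineligible places: 0%, 10%, 30%, 50%, 100%
- true OR = 1, with sites independent within a child

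**3. Formula.** Injury sites come only from eligible places, so their prevalence is pe. Control sites come from the whole route:

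pc = (1 − u) × pe + u × pi

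Expected OR = [pe/(1 − pe)] / [pc/(1 − pc)]

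Example, u = 5% and pi = 50%: pc = 0.95 × 0.10 + 0.05 × 0.50 = 0.120, so OR = 0.1111/0.1364 = 0.815.

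**4. Results for a feature with no true effect.**

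| Prevalence in ineligible places | u = 2% | u = 5% | u = 10% |
|---|---|---|---|
| 0% (rarer) | 1.02 | 1.06 | 1.12 |
| 10% (equal) | 1.00 | 1.00 | 1.00 |
| 30% | 0.96 | 0.90 | 0.82 |
| 50% | 0.92 | 0.82 | 0.68 |
| 100% (extreme) | 0.83 | 0.66 | 0.47 |

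In the 50% row, the approximate chance of a false significant result with 837 injury and 1674 control sites is 9%, 32% and 82%.

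**5. Number of sites affected.** The expected number of control sites in excluded places is 1674 × u: about 33, 84 and 167. The matching number of injury sites is zero by construction.

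**6. Simulation check.** A 1:2 conditional logistic regression was run with 837 sets, 60 runs per setting, an ineligible share that varied between children, and pi = 50%. The average OR for a null feature was 0.80 at u = 5% and 0.65 at u = 10%. With controls restricted to eligible places it was 0.98 and 1.01. A true OR of 1.5 shrank to about 1.24 at u = 5%; the formula gives 1.5 × 0.815 = 1.22.

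**7. Does the pre-injury wording remove the problem?** No. A route can cross private land or the city limit before the injury as well as after it. Limiting controls to the pre-injury part takes away only the post-injury opportunities.

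**The case against.** The strongest objection is that the article is condensed. It does not say that a point on private land is kept, and handling an awkward point could belong in a field manual. Project 2D takes its design, exclusions, interview procedures and forms from an earlier adult study, whose site-selection rules are not shown and may already restrict controls. This counts against any claim that ineligible control sites have been or will be collected. It does not dispose of the point: the article states the selection rule in operational detail, down to the random proportions and how the second point is moved, and that rule differs from the stated injury-site criteria.

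The opportunity may also be small. Routes are drawn on maps of streets and off-street paths, so driveways and parking lots may add little measured distance. A child must live and be injured in the city, so an out-of-city stretch requires crossing the boundary on the same trip. Moving the second point to match an intersection may also bring it back to an eligible place. All of this stands and argues for a low ineligible share.

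A reader might infer that low-traffic or off-road features will look falsely protective. The documents do not support that in general. An ordinary street beyond the city limit is still an ordinary street, and the route-type coding follows the earlier study, so how a private site would be classified is unknown. The bias can be absent or reversed.

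A reader might also infer a bias as large as the smallest effect the study is sized for (OR 1.5, inverse 0.67). At a 5% ineligible share, with the feature at 10% of eligible places, that requires every ineligible place to carry the feature.

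**Conclusion.** The point holds as a mismatch between two stated rules. Applied as written, they allow a place to supply controls but never cases, and the resulting odds ratios are biased for any feature whose prevalence differs between eligible and excluded places. The direction depends on the feature.

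The size cannot be derived from the documents. Under the middle assumption (10% against 50% prevalence, null feature) the expected OR is about 0.92, 0.82 or 0.68 at 2%, 5% or 10% ineligible route. The values 0.83, 0.66 and 0.47 are the extreme case. At about 2% or less the bias is small unless the feature is heavily concentrated in excluded places.

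This should be fixed because the remedy is nearly free and no planned analysis would correct the bias. With the ineligible share undocumented and the earlier study's procedures not shown, the documents do not support calling it a critical flaw.

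**What to change.** 1. In Project 2D, Interview and site selection, add that a control site must meet the same location criteria as an injury site: off private property and inside a participating city. Redraw any point that fails, checking the second point after it has been moved for intersection status. Report the number redrawn. If the inherited procedures already do this, say so.
2. For trips already mapped, drop ineligible control sites before fitting the conditional logistic model, or at least do so as a sensitivity analysis, and report how many were dropped. That count also gives a direct indication of the ineligible share.
3. Reconcile the pre-injury wording in the Abstract and the Project 2D Study design section with the whole-trip mapping in Interview and site selection, so that one control window is defined.

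The cost is a sentence or two, some redraws and, for trips already mapped, some lost control sites. A child who loses both controls drops out of the conditional analysis. The target of 837 injuries is unchanged.

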### Data collection

#### Interview and site selection

We will train a research assistant to conduct the interview using a semi-structured questionnaire to map the route of the injured bicyclist on the injury trip, including any trip continuation after the injury event. Detailed paper maps (including streets and off-street paths) will be used to identify the trip route and injury site. Using a digital map wheel, we will estimate the trip distance and multiply it by two randomly generated proportions to select two control sites along the route. The second of these points will be moved either forward or backward along the route (depending on participants study specific identification number) to match the intersection/non-intersection status of the injury site. We will ask questions on the circumstances of the injury event and characteristics of the injury and control sites on the trip such as street surface conditions, light conditions, presence of construction, and estimated speed. We will also collect data on personal characteristics (age, sex, bicycling experience etc.) and trip characteristics (type of bicycle, clothing colour, weather, time of day) for secondary analyses; the case-crossoverapproach inherently controls for these factors.

We will use the interview procedures and data collection forms that Teschke et al. used with adult bicyclists [24]. Our collaborators with expertise in child and youth injury prevention will modify the interview questions to ensure they were suitable for children and youth. The questionnaire and modifications were pilot tested with additional revisions made prior to initiation of the project.

Given that some children and youth will have mild to severe brain injuries, and that some information may come from very young children, the interviewer will record the source of the interview (child, parent, other proxy respondent, etc.) and rate their confidence in the quality of the interviewee’s description and recall of the bicycling route and site characteristics. We will conduct sensitivity analyses based on the interviewer’s trust in the information quality.

#### Site observations

A trained research assistant blinded to injury/control site status will visit the injury and control sites to conduct structured site observations using a site observation form. Additional research assistants will be available in each municipality in the summer (May–August: high volume for paediatric ED bicycle injuries). Observations will be made as close as possible to the time of the injury event (i.e., season, time of day, weekday versus weekend). The information captured will vary according to route type (roadway, off-road, intersection, etc.). For example, off-road site details include type of path (e.g., pedestrian only, multi-use), surface characteristics (e.g., asphalt, grass), one- or two-way traffic, posted bicycle speed limits, etc.; on-road site details include one or two-way motor vehicle traffic, parking, etc. Intersection details include traffic control devices, intersection features, etc. In addition, we will capture general site details such as slope (Clinometer with Percent and Degree Scales), route visibility (measuring wheel), and the average speed of up to 5 motor vehicles (velocity speed gun). The site observation form will restrict most observations to directly at the site (within 5 m), but some items refer to nearby areas (e.g., features present on the road (within 50 m). The site observation approach has undergone extensive reliability testing with site feature Kappa values of 0.73 to 1.0 [24].

### Data analysis

Route types will be classified into categories consistent with Teschke et al. [24] We will compare personal characteristics by age group: child (< 13 years old) and youth (13–17 years old) consistent with age categories used in our prior bicycling injury research [14, 59]. We will compare the characteristics of the injury and control sites accounting for the fact that we have matched data (i.e., the same subject contributes the injury and control sites along a given route) [60]. We will use conditional logistic regression analysis to examine the route characteristics related to bicycling injuries. We will add no more independent variables than 10% of the number of discordant pairs (case site location characteristics different than control site location characteristics) [61]. We have used this analytic approach in our previous work [62]. Multiple imputation analysis will be used to assess the influence of missing data on effect estimates [63].

#### Sample size

Based on our prior work [14, 64, 65] approximately 49% of bicyclists will meet eligibility criteria (injured in an urban location) and will agree to participate. Public Health Agency of Canada injury surveillance data [66] for 2013 indicated there were 1139 child and youth bicycling injuries at the study EDs (Email Communication, [name], Injury Section, Public Health Agency of Canada, June 29, 2016). This number would result in approximately 837 (1139*49% = 558 *1.5 years) eligible injuries from May, 2017-October, 2018. With a sample of 837 injury and matched control sites for each individual, we will be able to detect odds ratios as low as 1.5 with 80% power (0.05 significance level) for a control site exposure prevalence ranging from 10% through 70% [67]. Of note, in the study by Teschke et al. [24], the prevalence of various infrastructure types ranged from 1% (major street with parked cars, shared lane) to 33.5% (downhill grade).

#### Anticipated concerns

Child/youth ability to remember route information may vary. We will have a rating of the interviewer’s confidence in the child/parent description of the site and will also compare this information with site observation data. We will use multiple imputation methods for missing data.

It is possible that some site characteristics may change after the injury (e.g., construction sites). We would expect this potential misclassification to affect both injury and control sites equally, resulting in a bias to the null. We will also ask our municipal partners whether changes were made to these sites.

##### Objective 3

To identify implementation strategies for built environment change at the municipal level to encourage active transportation

##### Project 3A

To identify the facilitators and barriers for implementing built environment change at the municipal level

### Study design

We will conduct a multi-case, mixed-methods study in order to identify facilitators and barriers for implementing built environment changes affecting child pedestrian and bicyclist safety and active transportation at the municipal level. To do this, we will conduct: 1) An environmental scan (that includes a literature review), 2) Key informant interviews, 3) Focus groups, and 4) A national survey. We will conduct an environmental scan of publicly available information (e.g. information gathered from a literature review and municipal documents that outline processes for built environment) and use the synthesized research information from literature reviews of effective built environment interventions. This will inform the development of interview guides for key informants and focus groups and for the national survey.

### Location and participants

We will collect information in environmental scans from each municipality included in this study (Vancouver, Calgary, Toronto, Montreal). Stakeholders involved in the interviews will be representatives from the four municipalities. Key informants and focus group participants will include school staff, school board representatives, school trustees, municipal staff, city councilors, transit authorities, police, provincial transportation authorities, parents, children from each municipality that were/are involved in the implementation of built environment change. Focus group participants include 8–15 stakeholders from each municipality. Focus groups will be used to discuss perceived effects of built environment changes on active transportation and child pedestrian and bicyclist injury prevention, as well as the processes used for case specific built environment changes. Survey participants will include relevant stakeholders from our study municipalities and from other municipalities that have been involved in the implementation of built environment changes. This information will provide the research team with perspectives of broad implementation issues in other municipalities across Canada.

